### Study Objectives

The main objective of the study is to evaluate the impact of a 21-day school program on children’s oral health. The primary objective is to evaluate the impact on knowledge, behavior, and toothbrushing habits in school children after a 21-day school program and compare with baseline and control group. Subsequent objectives will examine the impact on oral health, durability of the intervention, and any wider benefits on parent/carer and child well-being. The specifics of the objectives are outlined in Textbox 1.

Study objectives.Primary: measure the impact on knowledge, behavior, and toothbrushing habits in school children after a 21-day school program and compare with baseline and control groupSecondary: measure the impact on oral health via plaque levels at baseline and after a 21-day school program with children and compare with children in their control groupTertiary: evaluate the longer term impact of the 21-day program on knowledge, behavior, and oral health in children after a period of 8 weeks and 24 weeks (ie, approximately 7 months in total)Quaternary: provide evidence that the 21-day school program is effective in getting parents and carers to also improve their brushing habits and to brush day and nightQuinary: measure the change in quality of life, well-being, and social measures of school children after a 21-day oral health program

## Methods

### Intervention

Children participating in the 21-day BDN school program are each provided with toothpaste and a toothbrush and follow brushing instruction, supervised brushing, and the singing of songs to facilitate learning the importance of brushing day and night, with stickers and calendars to track progress. A celebration is held at the end of the program with certificates and rewards. The program is supported by colorful materials with bespoke cartoon characters. Parents are provided with educational leaflets.

### Study Design

This study is a 2-arm, superiority cluster randomized trial. Clusters in this study are infant and junior schools in Indonesia and Nigeria. Schools will be matched into pairs by location and then randomized to intervention and control groups using a randomization table.

The study will look to recruit children aged 6 to 9 years in school grades 1, 2, and 3 to participate in the study. Children who assent to take part in the study (see Multimedia Appendix 2 for form), meet the selection criteria, and have the informed consent of their parents (see Multimedia Appendix 3 for form) will be enrolled in the study. The study flowchart is shown in Figure 1.

The T0 (baseline), T0+21 (end of 21-day intervention), T1 (8 weeks after the end of the intervention), and T2 (24 weeks after the end of the intervention) data collection time points will consist of questionnaire completion and a clinical assessment of plaque level evaluation using the Simplified Oral Hygiene Index (OHI-S) and an additional caries evaluation at T0 and T2 using the Decayed, Missing, and Filled Teeth index (DMFT). For the control group, the same flowchart will be followed, but the “Start 21-day BDN program/Finish 21-day BDN program” is replaced by only providing toothpaste and toothbrushes to school children.

The delivery of the intervention program relies on Unilever materials including toothpaste and toothbrushes as well as all the necessary educational materials. These materials are produced and delivered by Unilever locally. Translations of the materials to a local language will be completed if necessary. Toothpaste provided in Indonesia will be a commercially available and marketed product manufactured by Unilever Indonesia containing 1450 ppm fluoride as 1.12% sodium monofluorophosphate in a chalk base (Pepsodent Anti-Cavity or similar). In Nigeria, a commercially available and marketed toothpaste sold by Unilever Nigeria containing 1450 ppm fluoride (0.32% sodium fluoride) in a silica abrasive (Pepsodent Cavity Fighter Gel or similar) will be provided.

**Figure 1 figure1:**
[figure not shown]
Study flowchart.

### Selection of Schools

This is a cluster randomization trial with schools being the clusters, randomized to intervention or control groups. Schools need to be matched in terms of setting (city, suburb, rural) and socioeconomic status. The sample size calculation determined the number of schools that would be required to detect a difference between the test and control groups. The response of interest is an improvement in brushing behavior.

For Nigeria, it is assumed that 30% of the children are already brushing twice a day [6]. The trial is designed to detect a minimum 35% difference in the number of children brushing day and night at day 22 between the intervention group and the control group. It is assumed that the control group will see a 20% increase in proportion of children brushing twice a day due to the free toothpaste and toothbrushes they are given (Hawthorne effect). The interclass correlation has been set low at 0.05 and 0.10 (ie, low interpupil correlation) as we do not expect the children to influence each other in their brushing behavior because brushing will be carried out at home.

For Indonesia, it is assumed that 84% of the children are already brushing twice a day [6]. The trial is designed to detect a minimum 30% difference in the number of children brushing day and night at day 22 between the intervention and control group. It is assumed that the control group will have 40% of children brushing twice per day as a result of the Hawthorne effect. Again, the interclass correlation has been set at 0.05.

Therefore, for both Nigeria and Indonesia, the target number of schools is 20 (10 intervention and 10 control schools) calculated using power 80% and a significance level of .05. This number of clusters should also be sufficient to detect a difference of 0.5 in the OHI-S (plaque) at the same power and significance level. About 30 children in each class, in each grade, are anticipated, and for each child, the participation of a parent completing the questionnaires at each time point will be requested.

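### The Indonesian sample-size inputs contradict one another: 84% brush twice daily at baseline, controls are put at 40%, and a 30% difference is to be detected, so the stated 80% power has no support

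*Protocol article*

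**What the plan says.** All the inputs are in the Selection of Schools section of the protocol article.

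- Baseline: "For Indonesia, it is assumed that 84% of the children are already brushing twice a day".
- Target, comparing the two arms: "The trial is designed to detect a minimum 30% difference in the number of children brushing day and night at day 22". The text does not say whether the 30% is absolute or relative.
- Control rate: "It is assumed that the control group will have 40% of children brushing twice per day as a result of the Hawthorne effect".
- Clustering: "Again, the interclass correlation has been set at 0.05".
- Result, for both countries: "the target number of schools is 20 (10 intervention and 10 control schools) calculated using power 80% and a significance level of .05".
- Cluster size: "About 30 children in each class, in each grade, are anticipated". No total per school is given.

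For Nigeria, the preceding paragraph starts from a 30% baseline and assumes a 20% increase among controls. It attributes that increase to the free toothpaste and toothbrushes and labels it the Hawthorne effect. Controls in both countries receive these supplies (Study Design).

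**The concern.** An effect that the section uses to raise the Nigerian control rate is used, one paragraph later, to explain an Indonesian control rate less than half the baseline. A 30-point gap is available only by starting from that 40%. From the 84% stated two sentences earlier it is out of reach.

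This matters for interpretation. Twice-daily brushing is the response on which the trial was sized, and reported brushing frequency is among the primary outcome variables (Table 2). If 84% is right, the effect used to justify the Indonesian schools cannot be observed there. A null result could then be read as adequately powered evidence against a 30-point benefit, when the design could easily miss the smaller gains that are possible. If 40% is right, the baseline is wrong. The text does not let a reader tell which.

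**Working it through.** **Inputs from the article:** baseline 84%; control rate 40%; difference 30%; ICC 0.05; 10 schools per arm; 80% power; significance level .05.

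**Assumptions of this check:** a two-sided test, no dropout, and m children per school between 30 (one class) and 90 (one class in each of three grades).

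**1. Can the inputs coexist?**
- Controls at 84%: the headroom is 100 − 84 = 16 points. A 30-point gain gives 114%; a 30% relative gain gives 84 × 1.3 = 109%.
- The 40% read as an increase: 84 + 40 = 124%, or 84 × 1.4 = 118%.
- The 40% read as the level: this contradicts both the 84% and the upward direction of the effect.

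**2. Is 10 schools per arm at 80% power reproduced?**

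Schools per arm = n × DE / m, where n is the per-arm size for individual randomisation (pooled two-proportion formula) and DE = 1 + (m − 1) × ICC.

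- DE at m = 30: 1 + 29 × 0.05 = 2.45. At m = 90: 1 + 89 × 0.05 = 5.45.
- 40% vs 70%: n = 42. Schools per arm = 42 × 2.45 / 30 = 3.4, or 42 × 5.45 / 90 = 2.5.
- 40% vs 52% (30% relative to 40%): 22.1 schools per arm at m = 30 and 16.4 at m = 90.

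Neither reading gives 10. For 40% vs 70%, a continuity correction (4.0 and 3.0), a one-sided test (2.7 and 2.0) and one added cluster per arm (4.2 and 3.4) do not give it either.

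**3. Power with the planned 10 schools per arm**

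Effective size per arm: n_eff = 10m / DE, that is 300 / 2.45 = 122 or 900 / 5.45 = 165. Standard error: SE = √{[p₁(1 − p₁) + p₂(1 − p₂)] / n_eff}. Power comes from the noncentral t distribution with 18 degrees of freedom and noncentrality (p₂ − p₁) / SE.

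Example, 84% vs 94% at m = 90: SE = √[(0.1344 + 0.0564) / 165.1] = 0.0340; noncentrality 0.10 / 0.0340 = 2.94; power 79%.

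| Control vs intervention | m = 30 | m = 90 |
|---|---|---|
| 40% vs 70% | 99.7% | 99.97% |
| 40% vs 52% | 44% | 55% |
| 84% vs 89% | 19% | 24% |
| 84% vs 92% | 45% | 57% |
| 84% vs 94% | 67% | 79% |

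**4. Smallest difference detectable at 80% power with controls at 84%**

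Solving the same expression for the difference gives 11.3 points at m = 30 and 10.1 points at m = 90. At ICC 0.10 it gives 13.5 and 12.7 points. That value is a sensitivity check only: the article mentions 0.10 for Nigeria, not for Indonesia. With 9 degrees of freedom, to respect the matched pairs, the ICC 0.05 figures become 11.9 and 10.6 points.

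**The case against.** The strongest defence is that the 40% may have a different denominator. The section names improvement in brushing behavior as the response of interest, and Study End Points speaks of a percentage of positive change. If 84% already brush twice daily, only 16% can improve. Suppose 40% of that group improve in control schools and 70% in intervention schools. Nothing is then impossible, and the Hawthorne effect works upward. One class of 30 contains 0.16 × 30 = 4.8 such children, so DE = 1 + 3.8 × 0.05 = 1.19. The requirement becomes about 9.7 schools per arm (unpooled variance, n = 39.2) to 10.4 (pooled, n = 42), which is close to the stated 10.

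That makes a wording error a possible explanation, but it does not rescue the text. The sentence refers to children brushing twice per day, not to improvers among the rest. The match needs exactly one class of 30 per school; with 90 per school the same reading gives 4.6 to 4.9 schools. It also does not reproduce 10 schools per arm for Nigeria.

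Other points on that side do stand as limits. Taken alone, 40% vs 70% is feasible; the contradiction lies in the combination. Unsupported power is not the same as low power, since the literal absolute reading is overpowered. The article also says that 20 schools suffice for a 0.5 difference in OHI-S, so the number of schools has a second stated ground. That ground concerns the secondary plaque outcome and does not support the brushing calculation. An analysis adjusted for baseline could also do somewhat better than the figures above.

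**Conclusion.** The concern holds. The 84%, the 40% and the 30% cannot all be true, nothing elsewhere in the article reconciles them, and no literal reading tried yields 10 schools per arm at 80% power with 30 to 90 children per school. Power at the planned size is above 99% if 40% vs 70% is meant and 44% to 55% if 40% vs 52% is meant. If 84% is the true control rate, only differences of about 10 to 11 points or more reach 80% power, and gains of 5 to 8 points would have 19% to 57% power. These figures rest on ICC 0.05, a two-sided 5% test, 18 degrees of freedom, no dropout and the assumed cluster sizes. The contradiction itself depends on none of them.

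**What to change.** Reconcile the 84% and the 40% in Selection of Schools, and say which is the expected proportion brushing twice daily and in which children.

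- If 84% is the baseline: set the control proportion at 84% or higher, remove the 30% difference, and state what 20 schools can detect. That is about 10 to 11 percentage points at ICC 0.05 with controls at 84%, with about 13 points at ICC 0.10 as a sensitivity value.
- If 40% is right: correct the 84%, and replace the 80% with the power that the stated difference gives.
- If the 40% refers to improvement among children not yet brushing twice daily: say so, and give that denominator.

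In every case, express the difference in percentage points and give the number of children per school.

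The cost is one rewritten paragraph. Recruitment was already under way when the article appeared; the correction itself adds no schools and does not alter conduct. If 84% is kept, the stated target effect becomes smaller and the claim about power less favourable, and the Indonesian result should be interpreted against that.

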## Introduction

### Prior Work

The Brush Day & Night (BDN) program is the result of a 12-year partnership between FDI World Dental Federation (FDI) and Unilever. It is an intense education activity designed to establish the habit of brushing day and night with a fluoride toothpaste. The program involves daily brushing instruction and includes free toothpaste and toothbrushes (see Multimedia Appendix 1 for more information).

The program was designed based on the theories of behavior change. Behavior change interventions and the formation of health promoting habits is thoroughly reviewed by Lally et al [1] and specifically in the context of interventions to improve tooth brushing by Claessen et al [2]. This and other research was crystallized into the Unilever 5 levers of change model [3], which is the foundation for the design of this particular intervention. The first step of the model is to identify barriers, triggers, and motivators to adopting a new behavior. Those insights are considered in designing a new behavioral intervention in 5 steps:

Make it understoodMake it easyMake it desirableMake it rewardingMake it a habit

This is a 21-day intervention, a duration chosen to reflect past research [4] that repetition of between 12 and 15 times is necessary to make a habit change, and 21 calendar days is 15 school days. The choice of schools within which to implement the program was influenced by the work of Pine et al [5] that states schools can be an optimum place for behavior change interventions where both parents and teachers may be involved in the intervention. The duration of 21 days was also chosen to avoid the program becoming overly onerous for the schools and teachers implementing the program.

Previous work has shown that the 21-day BDN program is effective in improving children’s toothbrushing knowledge and habits [6]. A study conducted in 10 countries with 7991 children aged between 2 and 12 years revealed that 25% more of the school children brushed their teeth twice a day at the close of the 21-day intervention. The program was found to be more effective among the 7 to 9 year age group.

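### Twenty schools per country at 80% power does not follow from the stated inputs in either country; taken as written they need about 1.5 to 4 schools per arm, not 10

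*Protocol article*

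**What the plan says.** All the inputs are in the protocol article, Methods, Selection of Schools.

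- **Nigeria.** "For Nigeria, it is assumed that 30% of the children are already brushing twice a day". The control group is expected to gain 20% from the free toothpaste and brushes. For the effect, "The trial is designed to detect a minimum 35% difference in the number of children brushing day and night at day 22", and the sentence goes on to place that difference between the intervention and control groups. On clustering, "The interclass correlation has been set low at 0.05 and 0.10 (ie, low interpupil correlation"); neither value is named as the one used.
- **Indonesia.** The baseline is 84% brushing twice a day. The control group is expected to be at 40%, attributed to a Hawthorne effect. The minimum difference between arms at day 22 is 30%, and the ICC is 0.05.
- **Both.** The section then concludes: "Therefore, for both Nigeria and Indonesia, the target number of schools is 20 (10 intervention and 10 control schools) calculated using power 80" percent and a significance level of .05. About 30 children are expected in each class in each grade. Study Design gives three grades.

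The section does not say whether the percentages are absolute or relative, how many children per school were assumed, or whether the test is one- or two-sided.

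**The concern.** The section presents the school number as the result of its inputs, so a reader should be able to get from one to the other. A 35-point or 30-point difference is very large for a binary outcome, and at ICCs of 0.05 to 0.10 it should need only a few schools. Two countries with different rates, differences and ICCs also arrive at exactly the same number.

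Brushing behaviour is the response used for sizing and part of the primary objective. If the stated power and the stated difference do not belong together, nobody can say what a null or borderline result excludes. The trial might be heavily overpowered for 35 points, or sized for a difference nearer 15 points that is never stated.

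**Working it through.** **Formulas** (two-sided 5%, 80% power, unpooled variance):

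- children per arm without clustering: n = (1.96 + 0.8416)² × [p1(1−p1) + p2(1−p2)] / (p1−p2)², where (2.8016)² = 7.849
- design effect: DE = 1 + (m−1) × ICC, with m children per school
- schools per arm: k = n × DE / m
- power with 10 schools per arm: Φ(|p1−p2| / √{[p1(1−p1) + p2(1−p2)] / (10m/DE)} − 1.96)

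**Assumptions not in the document.** The test is two-sided and there is no dropout. m runs from 30 (one class per school) to 90 (one class in each of three grades). DE is 2.45 (m = 30) and 5.45 (m = 90) at ICC 0.05, and 3.9 and 9.9 at ICC 0.10.

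**Step 1: try to reproduce 10 per arm from the text as written.** The Nigerian control rate is 30 + 20 = 50% if the increase is absolute, or 30 × 1.2 = 36% if relative. Adding 35 points gives 85% or 71%. Example: 50% vs 85% gives n = 7.849 × 0.3775 / 0.1225 = 24.2, and at m = 90, ICC 0.05, k = 24.2 × 5.45 / 90 = 1.46.

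| Rates | n | ICC | k (m = 90) | k (m = 30) | Power at 10 per arm |
|---|---|---|---|---|---|
| Nigeria 50 vs 85 | 24.2 | 0.05 | 1.5 | 2.0 | >99.9% |
| Nigeria 50 vs 85 | 24.2 | 0.10 | 2.7 | 3.1 | 99.9% or more |
| Nigeria 36 vs 71 | 27.9 | 0.05 | 1.7 | 2.3 | >99.9% |
| Nigeria 36 vs 71 | 27.9 | 0.10 | 3.1 | 3.6 | 99.6 to 99.9% |
| Indonesia 40 vs 70 | 39.2 | 0.05 | 2.4 | 3.2 | 99.9% or more |

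The pooled-variance formula raises the largest values to 4.0 (Nigeria) and 3.4 (Indonesia). A continuity correction raises the largest Nigerian value to 4.8. For 10 per arm to be the 80% answer, the ICC would have to be about 0.30 to 0.37 in Nigeria or 0.21 to 0.23 in Indonesia.

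**Step 2: two ICCs, one school number.** For any pair of rates, k is proportional to DE. Moving from ICC 0.05 to 0.10 multiplies the schools needed by 9.9/5.45 = 1.82 (m = 90) or 3.9/2.45 = 1.59 (m = 30). The same 10 per arm cannot be the 80% answer at both.

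**Step 3: which other readings give about 10 per arm?**

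- *Nigeria, 35% and 20% both as gains from baseline:* 65% vs 50%, m = 90. n = 7.849 × 0.4775 / 0.0225 = 166.6. At ICC 0.05, k = 10.1 and power is 80%. At ICC 0.10, k = 18.3 and power is 54%. (Pooled variance: 79.0% and 53.5%.)
- *Nigeria, 35% relative to a 50% control rate:* 67.5% vs 50%, m = 30. n = 7.849 × 0.4694 / 0.0306 = 120.3. At ICC 0.05, k = 9.8 and power is 81%. At ICC 0.10, k = 15.6 and power is 61%. (Pooled variance: 79.8% and 59.8%.)
- *Indonesia, 30% relative:* 52% vs 40% at ICC 0.05 needs 16 to 22 per arm, while the absolute reading needs 2.4 to 3.4. Neither gives 10.

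**Step 4: Indonesia's rates.** A fall from 84% to 40% in a control group given free toothpaste and brushes is not what a Hawthorne effect would produce. Reading 40% as a gain does not help: 84 + 40 = 124%, and 84 × 1.4 = 117.6%. If control children stayed at 84%, the largest possible between-arm gain would be 16 points, so a 30-point gain could not occur.

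**Step 5: what 10 schools per arm can detect at 80% power.** From a 50% control rate: 15 points (m = 90) to 17 points (m = 30) at ICC 0.05, and 20 to 22 points at ICC 0.10. From 40% at ICC 0.05: 15 to 18 points.

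**The case against.** The strongest defence is that the article condenses a fuller calculation, and some unstated input would restore 10 per arm. Sidedness, modest dropout, variance formula and continuity correction do not close a gap of this size. A t reference does not either: in the harshest as-written case (36% vs 71%, 30 per school, ICC 0.10, 9 df) power is still 98.4%. A very small cluster would do it. With 5 children per school, Indonesia needs 39.2 × 1.2 / 5 = 9.4 schools per arm, but that contradicts the roughly 30 children per class the same section expects. Omitted detail might excuse a missing input, but here the inputs and the result are both printed and disagree.

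A second defence is that, as written, the error is towards too much power, so the trial is safe. That holds only if the 35-point and 30-point differences are what the team intended. The printed school number suggests that they may not be.

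In the other direction, a reader might infer that the trial is underpowered, with 54% as its true power. The document does not support that. It states no 15-point target and no 90 children per school, and it puts the 35% between the arms, not from baseline. Nor is 50% vs 65% the only reading that gives 10 per arm: 50% vs 67.5% with 30 children per school does so too, with 61% at ICC 0.10. Both are inferred, and both concern Nigeria only, because Indonesia has no ICC of 0.10. Lower power still could be claimed from a paired test on 10 matched pairs, but that would charge the lost degrees of freedom without crediting any gain from matching, and the Statistical Analysis section fixes no such test.

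**Conclusion.** The sample-size statement is wrong as written in both countries. The stated inputs need about 1.5 to 4 schools per arm in Nigeria and 2.4 to 3.4 in Indonesia, against the stated 10, at which power exceeds 99% by the normal approximation. This rests on between-arm differences in percentage points, a two-sided test, no dropout and 30 to 90 children per school.

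Two further defects do not depend on those choices. One school number cannot give 80% power at both Nigerian ICCs, and Indonesia's 84% baseline and 40% control rate cannot both stand as explained. Which inputs actually produced 20 schools cannot be known from the document, so the power figures of 54% and 61% show why clarification matters and are not estimates of the trial's power.

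**What to change.** For each country, state the control and intervention proportions assumed at day 22 in absolute terms, the children per school, the ICC used and whether the test is two-sided. Say whether the 35%, 30% and 20% are differences between arms or gains from baseline. Reconcile Indonesia's 84% and 40%. Then restate the power, or the difference detectable at 80% power, that 10 schools per arm delivers at each ICC stated for that country.

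The trial team must supply the inputs actually used; the readings in the working are not replacement text. As a guide, from a 50% control rate the detectable difference is about 15 to 17 points at ICC 0.05 and 20 to 22 points at ICC 0.10, for 90 to 30 children per school.

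The change is to text only and adds no schools. Its cost is that the stated power at ICC 0.10 may become less favourable.
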